# Evaluating the uptake and effects of the computerized decision support system NHGDoc on quality of primary care: protocol for a large-scale cluster randomized controlled trial

**DOI:** 10.1186/s13012-014-0145-5

**Published:** 2014-10-17

**Keywords:** Clinical decision support, Clinical practice guidelines, Primary care, Process of care, Patient outcomes

## Abstract

**Background:**

Computerized decision support systems (CDSSs) are increasingly used to improve quality of care. There is evidence for moderate to large effects from randomized controlled trials (RCTs), but evidence on their effectiveness when implemented at a national level is lacking. In the Netherlands, the Dutch College of General Practitioners (NHG) initiated their successful guideline program already 30 years ago. NHGDoc, a CDSS based on these NHG guidelines, covering multiple disease areas for general practice, was developed in 2006 with the aim to improve quality of primary care. In this paper, a protocol is presented to evaluate the uptake and effects of NHGDoc.

**Methods:**

A cluster RCT will be conducted among 120 general practices in the Netherlands. Eligible general practices will be randomized to receive either the regular NHGDoc decision support modules (control arm) or the regular modules plus an additional module on heart failure (intervention arm). The heart failure module consists of patient-specific alerts concerning the treatment of patients with heart failure. The effect evaluation will focus on performance indicators (e.g., prescription behavior) as well as on patient outcomes (e.g., hospital admissions) relevant in the domain of heart failure. Additionally, a process evaluation will be conducted to gain insight into the barriers and facilitators that affect the uptake and impact of NHGDoc.

**Discussion:**

Results of this study will provide insight in the uptake and impact of a multiple-domain covering CDSS for primary care implemented by a national guideline organization to improve the quality of primary care. Whereas the trial focuses on a specific domain of care—heart failure—conclusions of this study will shed light on the functioning of CDSSs covering multiple disease areas for primary care, particularly as this study also explores the factors contributing to the system’s uptake and effectiveness.

**Trial registration:**

Clinical trials NCT01773057

**Electronic supplementary material:**

The online version of this article (doi:10.1186/s13012-014-0145-5) contains supplementary material, which is available to authorized users.

## Background

Clinical practice guidelines aim to improve quality of care, but their implementation in practice remains a challenge. Despite considerable efforts in improving guideline implementation, several reviews have shown that guidelines are only moderately effective in changing clinical practice [1,2]. A study in the US showed that only about half of the patients received care as recommended in the guidelines [3]. Similarly, in other countries, adherence to the guidelines among physicians is found to be suboptimal as well [4,5].

Computerized decision support systems (CDSSs) are one of the tools that can be used to improve the uptake of guidelines in practice. By linking characteristics of individual patients to a computerized medical knowledge base, they can provide patient-specific recommendations to healthcare providers during patient care [6]. To the extent that CDSSs are guideline-driven, i.e., if the content is directly derived from clinical practice guidelines, they have the potential to increase physicians’ adherence to guidelines and ultimately lead to improved patient outcomes.

Whereas CDSSs are increasingly being used in various healthcare settings, evidence is mainly retrieved from small-scale academic-driven experiments among selected groups of innovators. Definitive evidence on their effectiveness in large-scale practice-driven use of CDSSs remains to be established. Some studies have shown that CDSSs can improve medical practice, e.g., [6-9]. In a recent series of six systematic reviews [10], it was found that CDSSs improved the process of medical care in 52%–64% of studies across all six reviews. However, only 15%–31% of those reviews that evaluated patient outcomes showed a positive impact on patients’ health [11-17].

Moreover, CDSSs seem to have added value as a tool for improving quality of care when focusing on specific behaviors (e.g., drug dosing) [6,7] within well-defined areas of care. A large share of medical care, however, is delivered by primary care practitioners (PCPs), particularly in the Netherlands [18]. PCPs work in generic settings and are confronted with a variety of diseases. This setting necessitates CDSSs covering multiple disease areas. Thus far, little is known on the effectiveness of CDSSs in settings in which PCPs are exposed to various alerts within multiple domains of care.

In the Netherlands, the Dutch College of GPs (NHG) initiated their successful guideline program already 30 years ago [19]. In 2006, NHGDoc, a CDSS based on these NHG guidelines and covering multiple disease areas for general practice, was developed as a collaborative effort between the Dutch College of GPs (NHG) [19] and ExpertDoc [20], a private enterprise. The content of NHGDoc is directly derived from the NHG guidelines—the national prevailing guidelines for general practice. NHGDoc is gradually being implemented at a national level and is currently—at the onset of the trial—integrated into two out of eight electronic health record systems (EHRSs) used in Dutch general practice, covering about 25% of all general practices in the Netherlands.

The aim of the study outlined in this protocol is to evaluate the uptake and effectiveness of the CDSS NHGDoc on the quality of primary care in the Netherlands. More specifically, our study’s aims are as follows:To assess the effects of the CDSS NHGDoc on relevant performance indicators for the process of medical careTo assess the effects of the CDSS NHGDoc on patient outcomesTo gain insight into the determinants that affect the uptake and impact of NHGDoc

## Methods/design

### Study design

A two arm-cluster (before and after) RCT will be conducted with a follow-up period of 12 months. Randomization will take place at a practice level, i.e., general practices will be randomized to the control arm or the intervention arm rather than individual PCPs. This will be the preferred unit of allocation as the intervention (i.e., the NHGDoc module on heart failure) can only be implemented at the level of the practices. Moreover, this is done to avoid possible contamination between PCPs working within the same practice yet being allocated to different study groups [21].

This study has been designed and will be reported in accordance with the CONSORT statement [22,23] and its extension regarding cluster RCTs [24] (see Additional file 1).

### Setting

The study will be conducted within the Dutch primary care setting. In the Netherlands, there are approximately 5,000 general practices in which nearly 11,000 GPs are delivering care [25]. Almost all GPs are members of the Dutch College of General Practitioners (NHG). Since the late 1980s, the NHG has produced over 100 national clinical practice guidelines for general practice [19]. These NHG guidelines cover the vast majority of conditions and diseases frequently seen in general practice. Currently, eight of these guidelines have been integrated into NHGDoc, i.e., cardiovascular risk management, asthma/COPD, diabetes mellitus type II, thyroid disorders, viral hepatitis and other liver diseases, atrial fibrillation, and subfertility.

Additional to GPs, approximately 3,000 practice nurses (PNs) are delivering care in approximately 60% of the Dutch general practices. They are mainly responsible for regular checks of the chronically ill such as cardiovascular and asthma/COPD patients [26].

NHGDoc was developed in 2006 as a collaborative effort between the NHG [19] and ExpertDoc [20]. As the NHG is the owner of the system and is an organization highly appreciated among GPs, it was decided to introduce the name ‘NHGDoc’ to the CDSS. NHGDoc is at the time of recruiting practices for the study integrated into two (MicroHIS X and Promedico-ASP) out of eight EHRSs used in Dutch general practice. These two systems cover about 25% of all Dutch general practices.

### Participants

All general practices in the Netherlands that use either the EHRS MicroHIS X or Promedico-ASP and thus have NHGDoc at their disposal, will be invited to participate in the study (*n* = approximately 1,100). To invite general practices to participate in the study, a comprehensive recruitment plan will be executed. All general practices will be approached by ordinary post mail signed by the NHG as well as an email signed by the EHRS providers (MicroHIS X and Promedico-ASP) and their user associations (Orego and Atlas). Additionally, announcements about the evaluation study will be placed in several relevant Dutch journals, websites, newsletters, and through social media (i.e., Facebook, Twitter, and LinkedIn). In all messages, reference will be made to the website of the evaluation study (www.nhgdoc-evaluatie.nl) which presents information about the study as well as an online registration form for general practices. To enable blinding of participants and contrast between groups, the study is purposefully presented as a before-after study without a concurrent control group, rather than as a before-after RCT. Therefore, the participants will not be aware of the fact that they will be allocated at random to two different conditions.

In order to participate in the study, each general practice should fill out the online registration form. The applicant is asked to consent on behalf of all practice staff (GPs and PNs) that could potentially use NHGDoc. This is necessary as the intervention and data collection can only be implemented at the level of the practices. We will, however, be able to distinguish between different users in analyzing the study results.

### Intervention and comparisons

#### Control arm: regular NHGDoc decision support

General practices assigned to the control arm receive the regular NHGDoc decision support. These practices receive decision support with respect to all modules (NHG guidelines) that—at the onset of the trial—have been integrated into NHGDoc (see ‘Description of NHGDoc and its regular modules (control arm)’ section).

#### Description of NHGDoc and its regular modules (control arm)

NHGDoc is a CDSS integrated within the EHRS and based on the NHG guidelines, the prevailing guidelines for general practice in the Netherlands. It provides GPs and PNs evidence-based and patient-specific advices during consultation in terms of patient data registration, drug prescription, and management.

At the time of the onset of the trial, NHGDoc covered the following NHGDoc modules: cardiovascular risk management, asthma/COPD, diabetes mellitus type II, thyroid disorders, viral hepatitis and other liver diseases, atrial fibrillation, and subfertility. For each NHG guideline, key recommendations have been selected based on relevance of disease burden, room for improvement, and possibility to translate or normalize the recommendation into if-then rules. This selection of key recommendations is approved by representative experts of the guideline committees. Subsequently, the selected key recommendations are digitized into NHGDoc.

When the GP or PN opens a patient file in the EHRS, anonymous patient and performance data are sent to the NHGDoc server. The patient and performance data are compared to the digitized guideline recommendations and in the case of a discrepancy between current and advised care, an alert will be sent back to the GP or PN.

#### Intervention arm: regular modules plus additional module on heart failure

General practices allocated to the intervention arm will receive the same decision support modules as the control arm (see ‘Description of NHGDoc and its regular modules (control arm)’ section), extended with the NHGDoc module on heart failure, which will be activated at the onset of the trial (see ‘Basic elements/key recommendations of the NHGDoc module on heart failure (intervention arm)’ section). The reason we chose heart failure to be the subject of the trial was first of all of pragmatic nature; heart failure was one of the few modules that were to be implemented into NHGDoc in the year of the onset of the trial. In addition, we chose heart failure as it is a relatively common condition for which relatively large improvements (in terms of increasing or decreasing mortality and morbidity) are to be expected if healthcare providers adhere to the treatment guidelines, compared to other conditions [27-31].

#### Basic elements/key recommendations of the NHGDoc module on heart failure (intervention arm)

The NHGDoc module on heart failure is directly derived from the NHG guideline on heart failure [32]. It consists of three types of alerts:Alerts on heart failure in terms of registering the following patient data:clearance of creatinine;(serum) creatinine;(serum) potassium;(serum) sodium;patient weight;heart (frequency);blood pressure (systolic and diastolic).Alerts on heart failure in terms of prescribing (or adjusting the dose of) the following drugs:(lis)diuretics;ACE-inhibitor;AII antagonist;potassium suppletion;beta-blocker;aldosterone antagonist;digoxin.For example: Stop prescribing ACE-inhibitor because of the reduced clearance of creatinine and the increased serum potassium and check these values.Alerts on heart failure in terms of (paying attention to) the following management aspects such as:stop prescribing medication such as calcium antagonist, thiazolidinedione, disopyramide or a combination of ACE-inhibitor and AII antagonists;consider adjusting the dosage of medication when hypertension is increasing;consider use of NSAID;consider weight policy, e.g., discuss weight reduction and consider increasing the dosage of diureticum if weight increases with two kilogram or more within a short period of time;consider temporary restriction of fluids;advice to give up smoking;consider sleeping research and;consider referral to a cardiologist or nephrologist.

### Study measures

#### Outcomes

To select outcome measures for our evaluation study, we first identified previously validated indicators for heart failure [33]. Subsequently, we consulted an expert panel of general practitioners as well as specialists in the area of heart failure to select the outcome measures that are clinically most relevant for our study and that are suitable for quantitative evaluation. Outcomes will be measured during the year before the start of the intervention (baseline) and in the first year following the start of the intervention (follow-up). This resulted in the following primary and secondary outcome measures:

#### Primary outcome measures (per practice, per year):

➢ Prescribing of ACE-inhibitors/angiotensin II

Percentage of consultations in which a patient with heart failure was prescribed ACE-inhibitors/angiotensin II.➢ Prescribing of beta-blockers

Percentage of consultations in which a patient with heart failure was prescribed beta-blockers.➢ Prescribing of diuretics

Percentage of consultations in which a patient with heart failure was prescribed diuretics.

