#### Secondary outcome measures:

➢ Use of the system NHGDoc

Number of requests sent and alerts received for all patients; number of requests sent and alerts received for heart failure patients; percentage of opened alerts compared to the number received alerts; percentage of opened alerts compared to the number received alerts for heart failure patients; mean delivery time for an alert; number of practices that switched any module off; for each module, the number/percentage of practices with at least one user who switched the module off; and number of practices with at least one user who switched the module heart failure off (intervention group only).➢ Patient data registration

Percentage of consultations in which for a patient with heart failure, relevant patient data have been registered: clearance of creatinine (<12 mnd); (serum) creatinine (<12 mnd); (serum) potassium (<12 mnd); (serum) sodium (<12 mnd); patient weight (<6 mnd); heart (frequency) (<6 mnd); blood pressure (systolic and diastolic) (<6 mnd).➢ Hospital admissions

Number of hospital admissions of patients with heart failure.➢ All cause mortality

Number of patients with heart failure that died in the hospital.

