### Data collection

To investigate the effectiveness of NHGDoc, data will be collected from two sources: the NHGDoc server and Dutch Hospital Data.

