#### NHGDoc server

For the largest part of this study, existing data collection methods from the NHGDoc alert service that have been developed by ExpertDoc to generate CDSS alerts for NHGDoc will be used. These are all automated data extractions from electronic patient records available in the EHRS. The NHGDoc alert service only uses anonymized patient data, and data are only streamed and not stored. For this evaluation study, however, it is necessary to save the anonymous data for the follow-up period of a year. Therefore, ExpertDoc, the company that manages the data, will send the NHGDoc data on a monthly basis, secured with a log in code, to IQ healthcare. NHGDoc data include all alerts, and the anonymous patient data that generate the alerts.

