#### Dutch Hospital Data

To be able to detect the effects of NHGDoc on patient outcomes, we also use data from Dutch Hospital Data (DHD), a foundation that collects and manages data of Dutch hospitals. Based on the practice codes (practice AGB codes) of the participating practices in both arms, DHD selects relevant data with respect to hospital admissions and mortality of patients that are registered with ICD-code I50 of the ICD 10 and sends them, after anonymizing the dataset, to IQ healthcare.

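### The primary prescribing percentages weight each patient by a contact count that arises after randomisation and may respond to the heart failure alerts, so the arm difference can shift with no change in prescribing

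*Protocol article*

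**What the plan says.** In the Protocol article, the section on primary outcome measures defines three percentages per practice and per year, for ACE-inhibitors/angiotensin II, beta-blockers and diuretics. The second reads "Percentage of consultations in which a patient with heart failure was prescribed beta-blockers", and the other two have the same form. The patient data registration outcome, among the secondary measures, is also a percentage of consultations.

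On where the data come from, the Data collection section states that "data will be collected from two sources: the NHGDoc server and Dutch Hospital Data". For the second source, "DHD selects relevant data with respect to hospital admissions and mortality of patients", so it holds no primary care prescribing. That leaves the server. The description of NHGDoc and its regular modules gives the trigger: "When the GP or PN opens a patient file in the EHRS, anonymous patient and performance data are sent to the NHGDoc server". The NHGDoc server section gives the content: "NHGDoc data include all alerts, and the anonymous patient data that generate the alerts". The description of the system also places its "evidence-based and patient-specific advices during consultation".

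The Analysis section compares follow-up scores between arms, adjusted for baseline, using multilevel linear regression for the prescribing outcomes. It mentions patient-level and practice-level intercepts.

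**The concern.** The outcome is defined per consultation, while the event that sends data is the opening of a file. That difference draws attention to the denominator, and the denominator is where the lasting difficulty lies.

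A percentage of consultations, or of openings, counts each patient as often as that patient appears. The number of appearances is not fixed at randomisation. The heart failure module runs only in the intervention arm, and its alerts concern registering creatinine, potassium, sodium, weight, heart frequency and blood pressure, and starting, stopping or adjusting drugs. Acting on such an alert can plausibly bring a further opening or a further consultation. If the extra rows fall unevenly on treated and untreated patients, the arm's percentage changes although no prescription has changed.

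Baseline adjustment uses the year before activation. It cannot correct a change in frequency that begins with activation and affects one arm.

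**Working it through.** **Reference figures.** The plan gives no figure for openings or consultations per patient, so there is nothing of its own to reproduce here. The Sample size section gives the yardstick: beta-blockers 59% to 65% and ACE-inhibitors 63% to 69%, which is 6 points in each case.

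**Step 1: unweighted percentage.** Assume that true prescribing is the same in both arms, that each row repeats the patient's prescribing state, and that rows are evenly spread in the control arm. Let p be the true share of patients treated and k the ratio of rows per treated patient to rows per untreated patient in the intervention arm. Then

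observed = p·k / (p·k + 1 − p).

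For p = 0.59 and k = 1.1: 0.649 / (0.649 + 0.41) = 0.6128, a shift of +2.3 points with no effect. The values of k are assumptions.

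| k | Beta-blockers (59%) | ACE-inhibitors (63%) |
|---|---|---|
| 1.05 | +1.2 | +1.1 |
| 1.1 | +2.3 | +2.2 |
| 1.2 | +4.3 | +4.1 |
| 1.3 | +6.2 | +5.9 |

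If untreated patients have the 10% excess instead, k = 1/1.1 and the beta-blocker figure is 0.5364 / (0.5364 + 0.41) = 0.5668, a shift of −2.3 points.

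**Step 2: the same with a patient-level intercept on row-level data.** In a linear random-intercept model, a patient with n rows gets a weight of roughly n / (1 + (n − 1)ρ), where ρ is the within-patient correlation. Assume 10 rows per untreated patient. For k = 1.3 (13 rows per treated patient) and ρ = 0.3, the weights are 10/3.7 = 2.703 and 13/4.6 = 2.826. Their ratio is 1.046, and 0.59 × 1.046 / (0.59 × 1.046 + 0.41) = 0.601.

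| ρ | k = 1.1 (11 vs 10 rows) | k = 1.3 (13 vs 10 rows) |
|---|---|---|
| 0 | +2.3 | +6.2 |
| 0.3 | +0.4 | +1.1 |
| 0.5 | +0.2 | +0.5 |

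At ρ = 0.9, the k = 1.3 shift is +0.06. With fewer rows (6.5 vs 5, k = 1.3), the shift is +1.8 at ρ = 0.3 and +0.9 at ρ = 0.5.

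**Step 3: a second model for the direction.** Suppose that a share f of rows came from openings outside consultations, with a percentage q prescribed in them. Then observed = (1 − f)p + f·q. Take f = 20% in control and 30% in intervention, with p = 59% in both arms. The spurious difference is −0.059 + 0.10·q: −5.9 points at q = 0, −2.9 at q = 30%, 0 at q = 59% and +4.1 at q = 100%. Both f and q are assumptions, and the article does not show that such rows are counted. The model confirms that either sign is possible and that there is no shift when the extra rows match the arm's own rate.

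**The case against.** A reader might infer that the server stores one row per opening and that laboratory results, repeat prescriptions and reopened files therefore enter the primary percentages. The article does not support that. It says that data are sent on opening, not what becomes a row. It also says of the server data that "These are all automated data extractions from electronic patient records available in the EHRS", so a contact date or type could be among the extracted fields. A rule for recognising consultations could sit in the full protocol or the SAP, and its absence from a journal article is not a fault. Nor does the system-use measure "number of requests sent and alerts received for heart failure patients" show substitution. Requests and consultations are named separately, which suggests that the authors distinguish them.

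A reader might also infer a bias close to the planned 6-point effect, in favour of the intervention. That is not supported either. No value of k is documented. The registration alerts are not limited to treated patients, and prescribing alerts may prompt contacts for untreated ones, so the sign is open. If each row repeats a patient's prescribing state, ρ is high and a patient-level intercept removes most of the shift, as step 2 shows.

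This last argument stands only in part. It needs the intercept to be fitted to row-level prescribing data. The Analysis section mentions patient-level intercepts just after the mortality model, while the primary outcomes are headed as per practice and per year. If rows are first reduced to a practice percentage, no patient weighting applies.

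It is also fair to say that frequency weighting belongs to any per-consultation denominator, even a perfectly recorded one. That makes the point more general without answering it.

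**Conclusion.** The point holds as a vulnerability of the primary comparison, not as a demonstrated bias. The denominator of all three primary outcomes accrues after randomisation. It may respond to alerts given in one arm only, and adjustment for the baseline year does not correct this. The shift can go either way and its size is unknown. It ranges from close to zero, with a patient-level intercept and high within-patient correlation, to 2.3 points for beta-blockers at an assumed 10% imbalance in an unweighted percentage. It disappears if the extra rows have the same prescribed percentage as the rest of the arm. The case for acting is that the safeguard is cheap, not that harm has been shown.

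**What to change.** Leave the three primary outcomes in place and make three additions:

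1. Collapse server records to at most one per patient per calendar day. This removes same-day repeats. It does not remove separate days on which a file was opened without a consultation, so it is not enough alone.
2. Add a sensitivity analysis of each primary outcome with one record per heart failure patient per year, for example the last. The result then depends on whether a file was opened in the year, not on how often the file was opened or the patient was seen.
3. Report openings per heart failure patient by arm, so that readers can see whether the count responded to the module.

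No new data collection should be needed. The records are already sent monthly, and the planned patient-level intercepts presuppose that a patient's records can be linked. The Trial status section says that no cleaning or analysis had been done at submission, so these rules could still be fixed beforehand. The cost is fewer rows and a little more analysis work. Little precision should be lost, because repeated rows for one patient on one day add almost no information.
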